The 3D T1 structure data analysis will be performed with FSL tools (FMRIB Software Library) [71]. SIENAX (part of FSL 5.0) [72] will be used to obtain the volumes of neocortical GM, total GM, and WM. The normalised volumes of subcortical regions such as hippocampus and thalamus will be estimated from FMRIB’s integrated registration and segmentation tool (part of FSL 5.0, FMRIB Software Library) [73]. The cortical thickness at each vertex will be obtained using FreeSurfer (http://surfer.nmr.mgh.harvard.edu). DTI data-processing pipeline will follow the diffusion toolbox in FSL to obtain FA and MD images, and voxelwise tract-based spatial statistics method will be applied to examine FA/MD changes. For the resting-state fMRI data, preprocessing and functional connectivity analyses will be performed with SPM12 software (SPM12, Wellcome Department of Imaging Neuroscience, London, UK; http://www.fil.ion.ucl.ac.uk/spm/) by using MATLAB 2013b (Mathworks, Inc., Natick, MA, USA).

### Outcome measurements

The clinical outcome will be measured by six self-report questionnaires at baseline and the end of 6 and 12 weeks of treatment, followed by 12, 36, and 48 weeks of follow-up. The responses can reflect the degree of pain, sensation, emotion, and quality of life.

#### Primary outcome measurement

The primary outcome measurement is VAS [74]. VAS is used to assess the current degree of pain. VAS is a 10-point scale selected to quantitatively measure the level of KOA pain during the study, for which 0 means no pain and 10 means unbearable pain. The VAS mean scores will be assessed by repeated longitudinal analysis. The single timepoint of the primary interest for the comparison is week 12.

#### Secondary outcome measurements

The secondary outcomes are Short-Form McGill Pain Questionnaire (SF-MPQ) [75], Western Ontario and McMaster Universities Osteoarthritis Index (WOMAC) [76], and the 36-Item Short Form Health Survey (SF-36) [77]. SF-MPQ assesses the intensity and component of knee pain, WOMAC will be used to assess the intensity of KOA symptoms in multiple dimensions. SF-36 will be used to measure the Quality of life (QoL) of the participants. HAMA will be used to measure the level of anxiety of the participants. HAMD will be used to measure the depression level of the participants.

SF-MPQ is used to evaluate the pain, emotion, and psychological status of patients with KOA. It primarily comprises a 15-descriptor (11 sensory and 4 affective) rating on an intensity scale as follows: 0 = none, 1 = mild, 2 = moderate, and 3 = severe. A higher total score indicates more severe pain. The WOMAC is a self-administered questionnaire comprising 24 items divided into three subscales: pain (5 items), stiffness (2 items), and physical function (17 items). These measurements will be used to evaluate the symptom and quality of life improvement. A repeated longitudinal analysis will be used to evaluate the SF-MPQ mean scores.

Furthermore, to investigate the influence of emotional state on the brain activity, HAMD [78] and HAMA [79] will be used.

Most items of the HAMD adopt the 5-level scoring method of 0–4 points. The standard of each level as follows: 0 = none; 1 = mild; 2 = moderate; 3 = severe; 4 = extremely severe. A few items adopt the 3-level scoring method of 0–2 points, and the grading standard as follows: 0 = none; 1 = mild to moderate; 2 = severe. The total score of HAMD is 78. A total score less than 8 means normal. A total score of 8–20 means possible mild depression. A total score of 20–35 means possible depression. A total score greater than 35 means severe depression. A repeated longitudinal analysis will be used to evaluate the HAMD mean scores.

The total score of HAMA can better reflect the severity of anxiety symptoms. The total score can be used to evaluate the severity of anxiety symptoms and the effect of various drugs and psychological intervention in patients with anxiety and depression. According to the data provided by the China scale collaboration group, a total score ≥29 means possible serious anxiety, ≥21 means possible obvious anxiety, ≥14 means anxiety, ≥7 indicates possible anxiety, and <7 means no anxiety symptoms. A repeated longitudinal analysis will also be used to evaluate the HAMA mean scores.

### Data collection and monitoring

The screeners will collect data on the baseline characteristics when the patients are recruited. CRFs include observation and scanning time points, outcome measures, adverse events, and safety evaluations. Doctors are blinded to evaluate various clinical pain indicators and fill-in relevant information timely and accurately according to the CRF requirement. Only outcome assessors can access the CRFs and perform double-data entry. Then, two data administrators, who are beyond the research team and blinded to group allocation, will independently receive the completed CRF and enter them into an Excel database (Microsoft, Redmond, WA, USA). They are required to have completed rigorous training for the data monitoring. Then, they will enter the real-time data into the Chinese Clinical Trial Registration Center, in which the electronic data-management system will be used to track and monitor the test data in real-time in the Department of Science and Technology in Yueyang Hospital. During the test, data administrators can access and manage data. After the test, all researchers will have access to the data, and non-researchers will not have access.

### Statistical analyses

Clinical data will be analysed through the intention-to-treat assumption. For all outcomes, we use longitudinal models where participant outcomes and treatments are collected at a multiple follow-up times. Moreover, participants who meet the suspension criteria will be removed from the trial, and the modified intention-to-treat analysis will be adopted. For the missing data, several sensitivity analyses will be conducted to evaluate their effects on the results of the experiment. All analyses were performed with SPSS 21.0 statistical software (IBM, Armonk, NY, USA) by statisticians who are blinded to the group allocation.

The baseline characteristics will be expressed with descriptive statistics for the two groups, which are reported as the mean ± standard deviation. A Kolmogorov–Smirnov test with Lilliefors correction will be used to analyse all quantitative variables to determine whether they follow a normal distribution. Parametric statistics (Tukey test) or nonparametric statistics (Wilcoxon rank-sum test) will be used for the within- and between-group analyses in accordance with the results of the homogeneity and normality analyses. When the initial homogeneity and normality of data distribution are found, repeated-measure ANOVA will be implemented, or the Friedman test and Kruskal–Wallis test will be used when initial homogeneity but non-normality of data distribution is found, or only linear mixed model will be adjusted for age and gender if the initial homogeneity is not found. Adverse events in each group will be documented as percentage for safety assessments by using the chi-square test or Fisher’s exact test. Statistical significance is defined as *P* < 0.05, and the 95% confidence interval will be reported.

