### Suspension criteria

Are unsuitable to continue to participate in the study owing to adverse events or serious adverse events during the trialAre unsuitable to continue to participate in the study because of serious deterioration of disease or some complications and special physiological changesUses concomitant medication during the 12-week treatment period is a suspension criteria. Non-compliance to concomitant interventions will be monitored by daily dairies and WeChat queries.

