### Blinding

Participants and therapists will not be blinded to treatment allocation, because of the features of the Tuina treatment and the education intervention. For participants, their subjective consciousness will affect the outcomes, which is unavoidable. Nevertheless, the evaluators, data managers, and statisticians will be blinded to the group allocation in the outcome evaluation procedure and data analysis throughout the entire procedure to reduce the risk of bias. The data will not be accessible to the evaluators until the collection is finished.

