### Interventions

The participants will receive a total of 24 treatments in 12 weeks. The interventionists, who hold a PhD, must have at least 10 years of experience with Tuina treatment and be skillful in healthcare education for the participants. They are also required to have passed a clinical test to ensure consistency of the trial. The clinical test primarily includes the time of Tuina, the positioning of the treatment site, and the application of specific Tuina manipulation types. The standard operating procedures primarily include Tuina’s time, treatment site, and manipulation category, as well as the time and content of health education. In the process of Tuina or Education intervention, the two groups will not allow any concomitant medications or other interventions. However, concomitant medications or other interventions can be used during subsequent follow-up, and the treatment will be recorded in detail.

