### Concomitant medications and other interventions

Patients with KOA will be instructed not to take any caffeine (e.g., tea and coffee), as well as other medications, weight-loss techniques, or physical activity to avoid confounding interference for the analgaesic effect of the intervention in the two groups. In cases of severe knee pain, ibuprofen (300 mg per capsule with sustained release) will be allowed as rescue medication and should be recorded on a knee-pain diary. After the end of the study, patients will be taught weight-loss techniques and physical activity. Patients are also asked to record the name, dose, date, frequency, and exact time of the medications used, as well as to report to the researcher if they take any medications during the study. Patient adherence will be maintained and monitored by good communication between the therapist and patient and by constant reminders.

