### Safety evaluation

The participants’ conditions will be carefully monitored by therapists during the process. If adverse events occur, participants with adverse events will stop participating in the trial. Immediate medical care will be provided to any participant experiencing adverse reactions that can lead to hospitalisation, for example fracture or coma. The details will be recorded in the case report forms (CRFs). The ethics committee will conduct an interim analysis and make a decision, which will be determined according to the severity of the adverse events of the participants. For example, conditions that lead to hospitalisation or even life-threatening are severer, whereas conditions such as muscle pain that can heal on their own are milder. Reports will be made to the ethics committee with statements and detailed reasons for trial suspension. The efficacy and safety of the intervention will be evaluated after 6 and 12 weeks of intervention and 48 weeks of subsequent follow-up. Evaluators can also be reformed with the clinical symptoms and AEs whenever the patients meet something important. After an adverse event is determined to be related to the trial plan, the research team will provide treatment costs and corresponding financial compensation for the damage inflicted by the trial plan.

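### The plan promises intention-to-treat but removes participants who meet post-randomisation, partly outcome-related suspension criteria, under an undefined modified ITT

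*Protocol article*

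**What the plan says.** The Statistical analyses section opens with the principle: "Clinical data will be analysed through the intention-to-treat assumption". Two sentences later it says that "participants who meet the suspension criteria will be removed from the trial, and the modified intention-to-treat analysis will be adopted". It does not say who belongs to the modified set. The next sentence adds: "For the missing data, several sensitivity analyses will be conducted to evaluate their effects on the results of the experiment".

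The Suspension criteria section lists three grounds: being unsuitable to continue because of adverse events, being unsuitable to continue because of serious deterioration or complications, and medication ("concomitant medication during the 12-week treatment period is a suspension criteria"). Withdrawal and loss of contact are listed separately, under Dropout criteria.

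Other sections bear on who would be removed:

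- Safety evaluation: "If adverse events occur, participants with adverse events will stop participating in the trial".
- Interventions: during treatment, "the two groups will not allow any concomitant medications or other interventions".
- Concomitant medications and other interventions: for severe knee pain, ibuprofen "will be allowed as rescue medication and should be recorded on a knee-pain diary".
- Blinding: "Participants and therapists will not be blinded to treatment allocation".

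The primary outcome is current pain on the VAS, with week 12 as the single time point of primary interest.

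**The concern.** Intention-to-treat compares the groups as randomised. Removing people for what happens to them after randomisation means that the groups compared at week 12 may no longer be those that randomisation made comparable.

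The reasons for removal are not neutral here. Serious deterioration and analgesic use can both follow from pain, which is the primary outcome, and the medication ground runs right up to the primary time point. Patients know their allocation, and the therapists, who also monitor patients for adverse events, know it too. The share removed, and the kind of patient removed, could therefore differ between arms. If Education loses more of its patients with poor pain results, a benefit of Tuina is understated. If Tuina loses more of them, the benefit is overstated.

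**Working it through.** **Reading the sections together**

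1. Statistical analyses names ITT, then removes suspended participants and adopts a modified ITT. Removal is the only thing that distinguishes the second from the first, so exclusion from the analysis is the natural reading.
2. All three suspension grounds can occur only once a patient is in the trial.
3. Suspension criteria ends participation for adverse events only where the patient is unsuitable to continue. The sentence in Safety evaluation carries no such limit, although the same section goes on to class self-healing muscle pain as milder.
4. Suspension criteria and Interventions bar medication during treatment, while the concomitant-medication section allows rescue medication. As written, permitted rescue use for severe pain could itself lead to removal.
5. Nothing says that suspended participants are followed to week 12.

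**Size of the possible bias**

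The plan has no figure of its own on this point to reproduce. From Sample size: expected VAS changes of 3 (Tuina) and 0.7 (Education), so a planned difference of 3 − 0.7 = 2.3, and SD σ = 2.1 in each group. Assumed, because the document gives neither: the share q removed in each arm, and the correlation ρ between the removal trigger and the VAS improvement.

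If improvement is normal and the worst share q on the trigger is removed, the mean improvement of those kept rises by ρ × σ × φ(z_q)/(1 − q).

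- q = 0.20: 0.2800/0.80 = 0.3500
- q = 0.05: 0.1031/0.95 = 0.1086
- Shift in the difference: ρ × 2.1 × (0.3500 − 0.1086) = ρ × 0.507

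| ρ | Shift (VAS points) | Share of 2.3 | Difference if Education loses 20% | Difference if Tuina loses 20% |
|---|---|---|---|---|
| 0.3 | 0.15 | 7% | 2.15 | 2.45 |
| 0.5 | 0.25 | 11% | 2.05 | 2.55 |
| 0.7 | 0.35 | 15% | 1.95 | 2.65 |
| 1.0 | 0.51 | 22% | 1.79 | 2.81 |

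With 20% removed from both arms by the same mechanism, the two terms cancel and the shift is 0.

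A simulation with no true difference, 30 randomised per arm and removal of 20% versus 5% gave a two-sided type I error of about 7% (ρ = 0.5), 10% (ρ = 0.7) and 17% (ρ = 1.0). With 20% removed from both arms (ρ = 0.5) it was 4.7%, close to the nominal 5%.

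**Does power require the removal?**

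No. With 30 per group, 2.3/(2.1 × √(2/30)) = 4.24, and 4.24 − 1.96 = 2.28, a power of about 98.9%. With 24 per group (20% lost), 3.79 − 1.96 = 1.83, about 96.7%. Both use the plan's own inputs and the normal approximation.

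**The case against.** The plan is not without safeguards. It announces sensitivity analyses for missing data and longitudinal models, so visits before removal may still contribute, and evaluators, data managers and statisticians are blinded. A reader might infer that nothing protects the comparison, and that goes too far. Still, the sensitivity analyses are unspecified, and no analysis can recover a week-12 score that was never taken. The linear mixed model, which could use incomplete series, is named only for the case where initial homogeneity is not found. Blinded evaluation does not stop unequal removal.

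The modified-ITT sentence can also be read as qualifying the opening one, and it does not literally say that earlier data from suspended participants are discarded. That is fair. Exclusion is the natural reading, but an inference, and the text should not leave it to one.

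A reader might also infer that the direction of bias could never be judged. Adverse events go into the case report forms, medication use is recorded in detail, and adverse events are summarised by group, so the likely direction could be discussed. What is lost is the size, because the scores are missing.

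Frequent or unequal removal is not established either. Entrants have mild radiographic change (Kellgren-Lawrence I-II) and have been off analgesics for a month. For brief, self-resolving soreness, a strong correlation with week-12 knee pain is implausible, so the lower rows of the table do not fit that ground for removal.

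**Conclusion.** The point stands. The section names one analysis principle and then states a rule that departs from it, leaves the resulting set undefined, and ties removal to events that arise after randomisation and are partly related to the primary outcome. This is a stated rule for the primary comparison, not a detail left to a later analysis plan.

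The bias could be nil or could reach about 0.5 VAS points: about 0 if removal is equal by the same mechanism, and about 0.15 to 0.5 (7-22% of the planned 2.3) at 20% versus 5% removed and correlations of 0.3 to 1.0. The SD and the planned difference are the document's. The removal rates and correlations are assumptions, and a correlation of 1.0 is an extreme. A reader might infer that the rule favours Tuina. The documents do not support that, because the sign depends on which arm loses more patients with poor results.

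**What to change.** - Delete the sentence on removal and modified ITT. Define the primary analysis set as all randomised participants, in the group to which they were allocated.
- Separate stopping the intervention from leaving the study. Unless consent is withdrawn, keep collecting the scheduled VAS scores from those who stop, and use them.
- Report the analysis without suspended participants as a labelled sensitivity analysis, with suspension counts and reasons by arm.
- The investigators must reconcile Suspension criteria with Safety evaluation on which adverse events end participation, and Suspension criteria and Interventions with the concomitant-medication section on medication during treatment. These are clinical decisions, and no rule is proposed here.

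The cost is a protocol amendment, notified to the steering and ethics committees while recruitment is under way, and a few extra self-report follow-ups. The sample size need not change.

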**Methods/design:**

This study will be a randomised controlled trial with a parallel-group design. A total of 60 eligible participants will be assigned to the Tuina group or healthcare education group (Education group) at 1:1 ratio using stratified randomisation with gender and age as factors. The interventions of both groups will last for 30 min per session and be conducted twice each week for 12 weeks. This study will primarily focus on pain evaluation assessed by detecting the changes in brain grey matter (GM) structure, white matter (WM) structure, and the cerebral functional connectivity (FC) elicited by Tuina treatment, e.g., thalamus, hippocampus, anterior cingulate gyrus, S1, insula, and periaqueductal grey subregions (PAG). The two groups of patients will be evaluated by clinical assessments and multimodal magnetic resonance imaging (MRI) to observe the alterations in the GM, WM, and FC of participants at the baseline and the end of 6 and 12 weeks’ treatment and still be evaluated by clinical assessments but not MRI for 48 weeks of follow-up. The visual analogue scale of current pain is the primary outcome. The Short-Form McGill Pain Questionnaire, Western Ontario and McMaster Universities Osteoarthritis Index, 36-Item Short Form Health Survey, Hamilton Depression Scale, and Hamilton Anxiety Scale will be used to evaluate the pain intensity, pain feeling, pain emotion, clinical symptoms, and quality of life, respectively. MRI assessments, clinical data evaluators, data managers, and statisticians will be blinded to the group allocation in the outcome evaluation procedure and data analysis to reduce the risk of bias. The repeated measures analysis of variance (2 groups × 6 time points ANOVA) will be used to analyse numerical variables of the clinical and neuroimaging data obtained in the study. *P*<0.05 will be the statistical significance level.

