### Study design

This is a single-centre and parallel randomised controlled trial. A total of 60 participants diagnosed with KOA based on the American College of Rheumatology (ACR) criteria (2019 revised version) [51] will be recruited as eligible patients. They will be randomly allocated into 2 equal groups with 30 patients per group, including a Tuina group and an Education group. The interventions of both groups will last for 30 min and be performed twice each week. The treatment period will be 12 weeks, and the follow-up period will be 48 weeks.

Outcome measurements and MRI scans will be assessed at the baseline and at 6 and 12 weeks after treatment, followed by 48 weeks of clinical follow-up. The changes in clinical variables and cerebral activity of each group will be analysed after data collection.

Evaluators and statisticians will be blinded to the group allocation during the procedure of outcome evaluation and data analysis [52, 53]. The trial flowchart and study design are shown in Figs. 1 and 2, respectively.

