### Sample size

Sample size is required to compare two group mean values. The calculation method of bilateral equality of two samples is adopted [56] for two groups of A = Tuina group and B = Education group. Suppose H0: μA−μB=0, H1: μA−μB≠0. According to previous relevant research and pre-experiment results [39, 57], we expect the VAS significant score difference between and after 12 weeks of Tuina as μA = 3, and the VAS score difference between and after healthcare education intervention as μB = 0.7, assuming that the standard deviation *σ* of the two groups is equal, i.e., *σ*=2.1. If we set *α*=0.05 as the type I error, *β*=0.10 as the type II error, and 1−*β*=0.90 as the power, the final result is that we need at least 25 samples in each group. For the primary outcome, VAS will be assessed at baseline and at the end of 6 and 12 weeks of treatment, followed by 12, 36, and 48 weeks of follow-up. The statistical significance is defined as *P* < 0.05, and the 95% confidence interval will be reported.

Many MRI studies have reported statistical significance with 12 to 21 patients per group [23, 58–60]. To have a powerful and repeatable statistical effect, we require 25 patients per group in this trial. Considering a 20% dropout rate and the possible excessive head motion during scanning, it will include 30 KOA participants in each group. In summary, we plan to enroll 60 participants, and each group will undergo MRI scans to investigate different central mechanisms between Tuina and healthcare education treatments.

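### The Wilcoxon rank-sum test is assigned to within-group comparisons of the same patients; pairwise visit comparisons made with it would be too conservative

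*Protocol article*

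**What the plan says.** The Statistical analyses section gives one pair of tests for two different tasks: "Parametric statistics (Tukey test) or nonparametric statistics (Wilcoxon rank-sum test) will be used for the within- and between-group analyses", the choice depending on checks of homogeneity and normality. It names no paired t test and no Wilcoxon signed-rank test.

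The data are repeated measurements. The Sample size section lists six visits per patient, the last three of them in the period after treatment: "VAS will be assessed at baseline and at the end of 6 and 12 weeks of treatment, followed by 12, 36, and 48 weeks of". Under Study design, "The changes in clinical variables and cerebral activity of each group will be analysed after data collection", so change within each arm is something the trial intends to look at.

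The same section also plans methods that respect the repeated measures:

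- a general statement: "For all outcomes, we use longitudinal models where participant outcomes and treatments are collected at a multiple follow-up times";
- if the data are homogeneous and normal: "When the initial homogeneity and normality of data distribution are found, repeated-measure ANOVA will be implemented";
- if they are homogeneous but not normal: "the Friedman test and Kruskal–Wallis test will be used when initial homogeneity but non-normality of data distribution is found";
- otherwise: "only linear mixed model will be adjusted for age and gender if the initial homogeneity is not found".

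The abstract adds: "The repeated measures analysis of variance (2 groups × 6 time points ANOVA) will be used to analyse numerical variables of the clinical and neuroimaging data". The article does not say how the sentence on Tukey and rank-sum relates to these models.

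**The concern.** The rank-sum test treats its two columns as different people. For Tuina against Education that is right. For week 12 against baseline within one arm it is not, because each patient contributes to both columns. The test then uses the variance of a difference between unrelated values. When visits are positively correlated, that variance is larger than the true variance of the mean change.

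The other methods named do not fully cover the gap. Friedman is an omnibus test over visits and does not say which visit differs from baseline. In the non-normal branch, the rank-sum test is the only two-sample test named for that question. In the parametric branch, Tukey is the only pairwise test named, and it is valid across visits only with the within-subject error term, which is not specified.

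At stake are the pairwise within-group results. Modest real changes would tend to be reported as not significant.

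**Working it through.** **Inputs.** From Sample size: expected VAS change 3 (Tuina) and 0.7 (Education), SD 2.1, alpha 0.05, 25 evaluable and 30 enrolled per arm. The correlation rho between two visits of one patient is not given; it is assumed to be 0.3, 0.5 or 0.7, with 0 as a reference. The protocol states no figure for within-group precision or power, so there is none to reproduce.

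**Step 1, standard errors.** With SD s at each visit and n patients:

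- independent-samples SE of the mean change = s·sqrt(2/n);
- correct paired SE = s·sqrt(2(1 − rho)/n);
- ratio = 1/sqrt(1 − rho) = 1.20, 1.41 and 1.83 at rho = 0.3, 0.5 and 0.7.

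**Step 2, approximate true size.** A test that uses the larger SE rejects only when the correctly scaled statistic exceeds 1.96 × ratio:

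- rho 0.3: 1.96 × 1.195 = 2.34, two-sided tail about 0.019;
- rho 0.5: 1.96 × 1.414 = 2.77, tail about 0.006;
- rho 0.7: 1.96 × 1.826 = 3.58, tail about 0.0004.

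**Step 3, simulation of the rank tests.** Correlated normal before-after values, SD 2.1 at each visit, 5,000 runs per cell, nominal two-sided 5%. Power is for a true fall of 0.7.

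| n | rho | Size, rank-sum | Size, signed-rank | Power, rank-sum | Power, signed-rank |
|---|---|---|---|---|---|
| 25 | 0 | 0.050 | 0.054 | 0.19 | 0.19 |
| 25 | 0.3 | 0.018 | 0.046 | 0.15 | 0.25 |
| 25 | 0.5 | 0.010 | 0.055 | 0.13 | 0.35 |
| 25 | 0.7 | 0.001 | 0.054 | 0.08 | 0.51 |
| 30 | 0 | 0.047 | 0.046 | 0.23 | 0.23 |
| 30 | 0.3 | 0.019 | 0.048 | 0.20 | 0.31 |
| 30 | 0.5 | 0.007 | 0.049 | 0.16 | 0.40 |
| 30 | 0.7 | 0.002 | 0.048 | 0.11 | 0.61 |

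The sizes agree with Step 2 apart from simulation error and small-sample effects. At zero correlation the two tests agree, so the gap is due to the ignored pairing.

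**Step 4, Tukey.** With two means Tukey equals the unpaired t test. At n = 30 and rho = 0.5 its size is 0.007 (paired t 0.052), and its power for 0.7 points is 0.17 (paired t 0.41). Over three visits (20,000 runs, equal correlations, n = 30, rho = 0.5), Tukey's familywise error is 0.003 with the independent-samples error term and 0.048 with the repeated-measures term. The error term decides whether the test is sound.

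**Step 5, the expected Tuina change.** For a 3-point fall (n = 25, rho 0.3 to 0.7, SD 2.1 taken either as the visit SD or as the SD of change), rank-sum power is at least 0.997. A change of that size would not be missed.

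**A caveat on the SD.** The protocol applies 2.1 to the change score. Step 3 uses it at each visit, which gives an SD of change of 2.1 × sqrt(2(1 − rho)): 2.48, 2.10 and 1.63 at rho = 0.3, 0.5 and 0.7. The two readings coincide at rho = 0.5, so those rows stay closest to the protocol's own figure.

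**The case against.** The strongest reply is that the sentence is loose wording in a plan that otherwise handles repeated measures correctly. Repeated-measures ANOVA, Friedman and the mixed model all account for the pairing. The outcome sections assign a repeated longitudinal analysis to VAS, SF-MPQ, HAMD and HAMA. Tukey is a natural follow-up to a repeated-measures ANOVA and holds its level with the proper error term. The hypothesis under Sample size is between groups and the time of primary interest is week 12, where the rank-sum test is legitimate.

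Most of this stands, and it limits the reach of the point. It does not remove the error: the rank-sum test is explicitly assigned to within-group work, no paired alternative is named, and nothing links that sentence to the models.

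A reader might infer more than the text supports:

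- *That every before-after p-value is wrong.* The other methods in the same section contradict this.
- *That MRI results suffer most.* The abstract assigns repeated-measures ANOVA to the neuroimaging data, and the MRI section names tract-based spatial statistics and SPM12. Nothing ties the rank-sum test to MRI summaries in particular, and no scan-to-scan correlation is given.
- *That significance in one arm only will be read as a treatment effect.* No section says so. That misreading is possible even with correct paired tests, so it is not a measure of this fault.

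**Conclusion.** The point holds as a narrow error in the named method. Pairwise within-group visit comparisons made with the rank-sum test, or with Tukey on an independent-samples error term, are miscalibrated in the conservative direction: under positive correlation they miss real change and do not create excess false positives. For 25 to 30 patients per arm and rho from 0.3 to 0.7, the rank-sum test's true size is about 2% down to 0.1%. Its power for a 0.7-point change is about 0.20 to 0.08, where the signed-rank test has 0.25 to 0.61. These figures rest on an assumed correlation, normal data and equal visit SDs of 2.1; the direction needs only a positive correlation.

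The primary inference is not threatened, and neither is detection of the expected Tuina change. This is a correction to secondary within-arm reporting, worth making because the sentence is wrong as written.

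**What to change.** In the Statistical analyses section:

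1. Restrict the rank-sum test to between-arm comparisons.
2. For within-group change from baseline, name contrasts from the planned repeated-measures or mixed model, using Tukey only with the within-subject error term. Alternatively, name paired t or Wilcoxon signed-rank tests.
3. Say how these pairwise comparisons follow the omnibus analyses in each branch.
4. State that within-group p-values are descriptive and that conclusions on Tuina rest on the between-arm difference.

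The cost is a few sentences. Data, visits, sample size and software stay the same.
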